#### 2.3.4. Randomization

An independent researcher who is unaware of the study characteristics will conduct the random assignment procedure. A computer-generated random number sequence (Sealed Envelope™ software version 1.21.0, London, UK), assigned to participants’ academic record number will be used to randomly designate participants to one of the two groups (IG or CG). Random permuted blocks will also be used to reduce the random sequence predictability and guarantee a 1:1 ratio. This sequence will be password-protected in a table and will be hidden from other researchers during the study.

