### 2.7. Study Procedure

Participants will be recruited over two weeks and via four channels. Information and informed consent that is mandatory for participation will be provided on the institution’s mobile app, in an institutional email and through two classroom sessions. Furthermore, information will be provided on informative posters on the electronic boards placed around the university premises.

After the two-week recruitment phase, all informed consent forms will be collected, and the inclusion/exclusion criteria applied. This will be conducted by a team researcher who will not take part in the intervention. Once the recruitment phase has been completed, students will be codified with their personal academic record number, and the intervention and control group will be randomly assigned. The intervention group will be divided into two groups (intervention group 1 and intervention group 2) according to session schedule preferences.

As shown in Figure 2, the following phases consist of the pre-intervention assessment for both groups, two behavioural–cognitive sessions with the intervention groups, and the post-intervention assessment. 

Ten Kronowise 3.0 devices will be acquiring data a whole week for each student, so the different phases will be staggered for the groups. This means that the intervention protocol will last a total of 16 weeks (see Figure 2).

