### 2.8. Data Analysis

For the statistical analysis, all variables will be coded by using IBM Statistics SPSS v.21 software (Chicago, USA) for Windows and revised twice. A protocol approach will be followed where missing data will not be included in the analysis.

All descriptive statistical parameters will be expressed as absolute (‘n’) and relative (‘%’) frequencies for each qualitative variable category. Quantitative variables will be analysed with the mean, median, and standard deviation to observe their behaviour at a confidence interval of 95%. Normal variable distribution will be analysed by using the Kolmogorov–Smirnov test with Shapiro–Wilk correction. 

A repeated measures ANOVA will be used to compare mean differences between the intervention and control groups over time, considering the time–group interaction effect. The size of the effect will be analysed based on Cohen’s d [40]: 0–0.3 low, >0.3–0.8 moderate, and >0.8 large effect size. Any incomplete questionnaires will be excluded from the analysis. Results will be considered statistically significant when *p* < 0.05.

The PROCESS macro will be used to examine the mediating effects of sleep quality on the relationship between attending the sleep intervention or not. This analysis uses linear regression to estimate indirect effects according to Hayes and Rockwood’s methods recommended for clinical studies and focuses on two measurement moments [41]. Post-treatment scores will be added as mediators, and baseline scores for the outcome variables and mediators will be added to the models as covariates. Least-square path analysis will be used and the bootstrap confidence interval (5000 permutations) will be applied to estimate indirect effects.

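### The planned time-by-group test is an unadjusted change-score contrast: take the baseline PSQI before allocation, adjust for baseline by ANCOVA, and correct the claim that permuted blocks reduce predictability

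*Protocol article*

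**What the plan says.** Section 2.3.4 (Randomization) of the protocol article has an independent researcher attach a computer-generated sequence to academic record numbers. It adds: "Random permuted blocks will also be used to reduce the random sequence predictability and guarantee a 1:1 ratio". It gives no block size and names no balancing factor. On concealment it says: "This sequence will be password-protected in a table and will be hidden from other researchers during the study".

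Section 2.7 (Study Procedure) gives the order of events. Recruitment lasts two weeks, then consent forms are collected and eligibility is applied. After that, "students will be codified with their personal academic record number, and the intervention and control group will be randomly assigned". Only then, "the following phases consist of the pre-intervention assessment for both groups". The wrist-device measurement is staggered, since "Ten Kronowise 3.0 devices will be acquiring data a whole week for each student".

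Section 2.3.5 (Blinding Design) states that participants cannot be blinded.

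Section 2.8 (Data Analysis) names the main comparison: "A repeated measures ANOVA will be used to compare mean differences between the intervention and control groups over time, considering the time–group interaction effect". Baseline scores appear as covariates only in the mediation models described later in that section.

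**The concern.** Three passages bear on how baseline sleep is handled.

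- **The reason given for blocking is wrong.** In a permuted block the last allocations are fixed by the earlier ones. Compared with simple randomisation, blocking therefore raises predictability.
- **The baseline is measured after assignment.** Students know their group when they fill in the first PSQI, so a self-reported baseline can be coloured by that knowledge. No baseline score is available to the person who allocates.
- **The main test does not adjust for baseline.** With one measurement before and one after, the time-by-group interaction is the between-arm difference in mean change. It subtracts the whole baseline value, although only a fraction r of it predicts the later value. In the one trial that is run, a chance baseline gap therefore moves the estimate in the opposite direction, and the contrast has a larger variance than it needs.

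At stake is precision in a 60-student pilot whose own Discussion says that the sample may be too small to show group differences.

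**Working it through.** **Inputs from the protocol article.** 60 students, 30 per arm (Abstract); two measurement times (section 2.5.1, Table 2); significance at p < 0.05 (section 2.8, taken as two-sided); ten devices, one week per student (section 2.7).

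**Assumptions, not in the document.** Block size 2, 4 or 6; d = 0.5 for the medium effect in section 2.3.3, which lies inside the moderate band of over 0.3 to 0.8 in section 2.8; pre-post correlation r = 0.5, with 0.3 to 0.7 as the range. Effects are in units of the outcome SD, taken as equal before and after.

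**1. The plan's own figure.** Section 2.3.3 derives 60 from a population of 70, 95% confidence and ±5%. n0 = 1.96² × 0.25 / 0.05² = 384.1, and n = 384.1 / (1 + 383.1/70) = 59.3, rounded up to 60. It reproduces. It is a survey-precision figure and says nothing about the power of the comparison.

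**2. Predictability.** Take a guesser who always names the arm that is behind. In a block of 4, the chance of being right at positions 1 to 4 is 1/2, 2/3, 2/3 and 1. The mean is 2.833/4 = 71%. Position 4 is always certain and position 3 is certain one time in three, so 1.333/4 = 33% of allocations are fully determined. Blocks of 2 give (0.5 + 1)/2 = 75%. By simulation, blocks of 6 give 68% and randomly varying sizes (4/6/8 or 2/4/6) give 68 to 70%. Simple randomisation gives 50%.

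**3. Chance baseline gap.** Its standard deviation is sqrt(2/30) = 0.258 SD. P(|gap| > 0.25 SD) = P(|Z| > 0.25/0.258) = P(|Z| > 0.97) = 33%. P(|gap| > 0.5 SD) is about 5%.

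**4. Carry-over.** Given a baseline gap g, the expected later gap without any effect is r × g. The change contrast therefore shifts by r × g - g = -(1 - r) × g. Simulation at r = 0.5 gives a slope of -0.50, against zero for ANCOVA.

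**5. Precision and power.** The variance of the change contrast is 2(1 - r) × 2/30; for ANCOVA it is (1 - r²) × 2/30. Their ratio is (1 + r)/2, which is below 1 for any r < 1. The standardised effects are d/sqrt(2(1 - r)) and d/sqrt(1 - r²). Power is from the noncentral t with 30 per arm.

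| r | Shift for a gap of 0.258 SD | Variance ratio | Power, change contrast | Power, ANCOVA |
|---|---|---|---|---|
| 0.3 | 0.18 SD | 0.65 | 36% | 51% |
| 0.5 | 0.13 SD | 0.75 | 48% | 59% |
| 0.7 | 0.08 SD | 0.85 | 69% | 76% |

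Simulation with allocation down an ID list and r = 0.5 agrees: about 48% and 59%.

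**6. What balancing would add.** Blocks of 4 down a list sorted by the baseline score cut the standard deviation of the gap to 0.04 SD; stratifying at the median gives 0.16 SD and an 11% chance of exceeding 0.25 SD. Power at r = 0.5 hardly moves under sorted blocking: 59% to 61% with ANCOVA in 6,000 simulated trials, and 48% to 48% with the change contrast.

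If the list is sorted but the test left unadjusted, the true variance is close to 0.75 × 2/30 = 0.050, while the test assumes 2/30 = 0.067. The critical value of 2.00 is then effectively 2.00/sqrt(0.75) = 2.31, so the type I error is about 2.4% instead of 5%. Baseline must therefore be in the model if balancing is used.

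**The case against.** **Predictability does no harm here.** A reader might infer that the blocks open the trial to selection bias. The document does not support this. Everyone is recruited, consented and screened before a single batch assignment, an independent researcher does it, and the sequence is hidden. A guesser has nothing to act on, and the guess rates rest on assumed block sizes. This objection stands in full. The 1:1 purpose is also sound: simple randomisation gives exactly 30:30 only 10% of the time.

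**Chance imbalance is not bias.** A reader might infer that leaving baseline sleep to chance biases the result. It does not. Over repeated randomisations the shift averages zero, and the standard error of the planned test already contains it: at r = 0.5 that standard error is sqrt(2 × 0.5 × 2/30) = 0.258, and the typical shift of 0.13 is half of it. What remains is a conditional point about the trial that is run, and a loss of precision that adjustment recovers.

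**Balancing is not free.** A reader might infer that the same blocks could balance baseline sleep at no cost, since the whole list is known. But under section 2.7 no sleep score exists at assignment. The PSQI would have to move forward. For the wrist device, 60/10 = 6 device-weeks would have to pass first. Not stratifying is a legitimate choice.

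**The repeated measures model already uses the baseline.** It does, but with a fixed coefficient of 1. This leaves the (1 - r) carry-over and the larger variance in place, so this objection does not remove the point.

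**Conclusion.** The predictability clause in section 2.3.4 is wrong and should be corrected, with little consequence for the trial. The substantive point is the order of assignment and baseline in section 2.7 together with the unadjusted interaction in section 2.8.

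A chance baseline gap above 0.25 SD occurs in about one trial in three. A typical gap moves the estimate by 0.08 to 0.18 SD for r from 0.7 down to 0.3. Adjusting for baseline removes that dependence and raises power by 7 to 15 percentage points over the same range, with 48% to 59% at r = 0.5.

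The 0.26 SD and 33% figures need only 30 per arm and approximate normality. The power figures rest on the assumed d and r, but the direction does not: with equal variances, ANCOVA has the smaller variance for every r below 1, apart from the one degree of freedom for the covariate. The order of events is read from the text of section 2.7; the two figures were not available.

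The document does not support calling the randomisation biased, the allocation exposed, or the lack of stratification an error.

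**What to change.** 1. **Section 2.3.4:** state that permuted blocks secure the 1:1 ratio, and that concealment and batch assignment after recruitment protect against prediction.
2. **Section 2.7 and Table 2:** collect the baseline PSQI before allocation, for example with the consent form. The device baseline can stay where it is.
3. **Section 2.8:** replace the unadjusted interaction by ANCOVA, with the post-intervention value as outcome, group as factor and that outcome's own baseline value as covariate. Use it for the PSQI and for the device measures. The section already enters baseline scores as covariates in its mediation models, so this is consistent with the rest of the plan.
4. **Optional:** stratify or block on the pre-allocation PSQI. This adds at most about 2 points of power and does not directly balance the device measure. If it is done, baseline PSQI must be in the model.

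**Cost.** No extra participants, staff or software. Allocation waits until the PSQI forms are in, and with staggered phases the PSQI baseline will be somewhat older when the sessions start.

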#### 2.3.5. Blinding Design

The study design does not allow the treatment assignment to be blind for the sleep experts facilitating the intervention and the participants. However, analysts will be blinded to the group-assigned treatment. To prevent interobserver variability bias, measurements will be taken by the same researcher in all cases.

### 2.4. Intervention

The intervention group will receive the programme sessions based on knowledge and cognitive–behavioural therapy to improve sleep quality, and the control group participants will continue with their normal routine. This programme will be developed with an active-constructive learning methodology in which students interact with the material so that their commitment to learning generates deeper knowledge [34]. For this reason, the intervention group will be subdivided into two groups of 10 participants. Reducing the group numbers in this way will enable greater participation and skills acquisition to improve sleep quality. This includes acquiring notions of chronobiology; locating nervous structures involved in biological rhythms, awareness of the existence of biological and social stimulus that determine human circadian rhythms and the importance of their synchronization, self-awareness of the chronotype; knowledge of variables that determine good sleep quality, knowledge of one’s own sleep pattern, routines that improve sleep quality, and resources to avoid variables that are detrimental to sleep quality.

The intervention will consist of face-to-face 90-min group sessions executed twice a week during November and December 2022. Each session will be divided into four parts focused on different aspects related to sleep quality. The first session will focus on knowledge of anatomical structures involved in sleep and their effect at a cognitive level. Students may also self-assess their sleep pattern so that strategies can be adapted to improve this pattern at the next session. The second session will focus on developing skills for better sleep hygiene, working on the students’ individual sleep routines and the results of their questionnaires and self-reports so that the elements of sleep hygiene can be adapted to each case. Table 1 specifies the objectives, session activities, required materials, and duration of the intervention.

The experts implementing the intervention will be a PhD candidate in biology specialized in the brain function of sleep, chronobiology, and circadian rhythms, and a registered nurse expert in health promotion and in healthy lifestyles education, who will conduct the particular part of the sessions related to sleep hygiene and nocturnal habits. 

### 2.5. Data Collection

The assessment process will include self-assessment questionnaires in which participants must answer questions on their perception related to sleep quality, socio-demographic aspects and lifestyle. 

#### 2.5.1. Dependent Variables

Sleep quality: Kronowise 3.0, Kronohealth, S.L., Spain. Kronowise 3.0 is a wrist device that conducts ambulatory circadian monitoring (ACM) based on thermometry, motor activity, and body position (TAP). TAP uses a combination of sensors in an algorithm that has been validated as ambulatory polysomnography. It was validated by comparing the assessment of these parameters with polysomnography in adults [35] and in patients diagnosed with Parkinson’s [36]. The device can measure sleep quality and circadian rhythms and identify circadian chronodisruption through parameters such as sleep latency, total sleep time (in minutes), sleep efficiency, number of awakenings and time between waking and sleep [35]. It can also identify sleep phases, nocturnal awakenings, temperature, exposure to infrared and blue light as well as other parameters such as time in bed, sleep onset, awake time, sleep interval, total time in movement, time in movement index, sleep acceleration index, wrist sleep temperature, napping time and napping frequency [36]. Participants will wear the device for seven consecutive days, including weekdays and weekends. Both groups will be measured twice (before and after the intervention), meaning that all participants will wear the device for a total of 14 days. Participants will be given appointments to fit and remove the devices. Information provided by the devices will be entered into the software that will be sent to Kronohealth S.L., Spain, which will produce reports of both measurements with the results of the parameters mentioned above, with the sleep quality indices established according to the device validation [35].Perceived sleep quality: Pittsburgh Sleep Quality Index, PSQI [37]. The PSQI contains 19 items and seven clinically important components related to sleep quality: subjective sleep quality, sleep latency, sleep duration, sleep efficiency, sleep disturbances, use of sleeping medication, and daytime dysfunction. Responses will be reported based on a Likert-type scale from 0 to 4. Overall sleep scores of 5 or less will be considered good quality, whereas scores of 5 or more will be considered low quality. The PSQI version that will be used is validated into the Spanish university framework by De la Vega et al. [37] with a Cronbach’s alpha of 0.72. The questionnaire will be given to all participants twice (before and immediately following the intervention).

#### 2.5.2. Independent Variables

All independent variables will be assessed before the intervention, except for the intervention group’s satisfaction questionnaire, which will be measured immediately afterward. Questionnaires on socio-demographic data and toxic habits are prepared ad hoc by the researchers.

*Socio-demographic data*: Date of birth, age in years, gender and sleep habits during the study (alone or accompanied).*Toxic habits*: Tobacco consumption (cigarettes/day), alcohol consumption (daily, weekly, sporadic, glasses), drug consumption (yes/no and type), and stimulating drink consumption (coffee, sugary drinks, energy drinks).*Physical exercise*: The International Physical Activity Questionnaire (IPAQ), simplified version [38]. The questionnaire consists of seven questions on frequency, duration and intensity of activity (moderate and intense) in the last seven days, as well as walking and sitting time during a working day. The questionnaire is classified into the following levels: low, moderate, and high physical activity. The higher the score, the more physically active the profile. The questionnaire is validated with a mean reliability of 0.80 [38].*Anthropometric variables*: Participants will report their weight (kg) and height (cm).*Satisfaction with the programme:* Using a questionnaire adapted to the proposal by Azpeleta et al. [39] with 10 questions and responses based on a Likert-type scale from 1 to 10. Greater satisfaction will be awarded a higher score.

Table 2 shows the data collection and monitoring instruments.

### 2.6. Ethical Considerations

This study will be conducted according to the principles established in the Declaration of Helsinki, in the Convention on Human Rights and Biomedicine (Oviedo Convention), and in the UNESCO Universal Declaration on the Human Genome and Human Rights. This study has been approved by the Research Ethics Committee of Camilo José Cela University (code: 06-22-UCJC-Sleep). 

All participants will be informed of the duration and characteristics of the study, and of its voluntary nature. After receiving a detailed explanation of the project, any doubts raised by participants will be answered before the students are asked to sign the informed consent form, which mandatorily must be signed to participate.

Participants may abandon the study at any time, with no further consequences. The highest professional conduct and absolute confidentiality will be always maintained, in accordance with European Regulation (EU) 2016/679 on the protection of natural persons and data processing and free movement, the Framework Act 3/2018 on personal data protection and the guarantee of digital rights, and Act 14/2007 on biomedical research. Only the principal researcher of the project will have access to the codified database.

### 2.7. Study Procedure

Participants will be recruited over two weeks and via four channels. Information and informed consent that is mandatory for participation will be provided on the institution’s mobile app, in an institutional email and through two classroom sessions. Furthermore, information will be provided on informative posters on the electronic boards placed around the university premises.

After the two-week recruitment phase, all informed consent forms will be collected, and the inclusion/exclusion criteria applied. This will be conducted by a team researcher who will not take part in the intervention. Once the recruitment phase has been completed, students will be codified with their personal academic record number, and the intervention and control group will be randomly assigned. The intervention group will be divided into two groups (intervention group 1 and intervention group 2) according to session schedule preferences.

As shown in Figure 2, the following phases consist of the pre-intervention assessment for both groups, two behavioural–cognitive sessions with the intervention groups, and the post-intervention assessment. 

Ten Kronowise 3.0 devices will be acquiring data a whole week for each student, so the different phases will be staggered for the groups. This means that the intervention protocol will last a total of 16 weeks (see Figure 2).

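### Baseline is measured after allocation in unblinded students, and measurement is staggered by group, so the baseline can depend on arm and, on the natural reading, the arms are measured in different weeks

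*Protocol article*

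**What the plan says.** Section 2.7 of the protocol article sets out the order of events. Recruitment closes, eligibility is checked, and then "the intervention and control group will be randomly assigned". The intervention group is next divided in two "according to session schedule preferences". Only after that does the text say that "the following phases consist of the pre-intervention assessment for both groups", followed by the sessions and the post-intervention assessment.

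Section 2.3.5 states: "The study design does not allow the treatment assignment to be blind for the sleep experts facilitating the intervention and the participants". Only the analysts are blinded.

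On the devices, section 2.7 says "Ten Kronowise 3.0 devices will be acquiring data a whole week for each student", "so the different phases will be staggered for the groups", and that "the intervention protocol will last a total of 16 weeks". It refers to Figure 2 for the week plan. Section 2.4 sets intervention subgroups of 10, and section 2.5.1 measures both arms before and after the intervention.

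Section 2.8 plans a repeated measures ANOVA with a time-by-group term, leaves missing data out of the analysis, and enters baseline scores as covariates in the mediation models. It names no term for calendar week or batch.

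**The concern.** There are two separate weaknesses.

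**Order.** The baseline is the reference for every comparison, so it should be unaffected by allocation. A student who knows that the programme is coming, or that it is not, may answer the PSQI differently, change habits while wearing the device, or not start at all. Randomisation does not protect a baseline taken after the arm is known. The damage carries forward, because baseline is both the first time point of the ANOVA and a covariate in the mediation models. Students lost after learning their arm also leave the analysis.

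**Calendar.** If whole groups take turns with the devices, intervention and control students are measured in different weeks between October and February. It is an assumption, not a statement in the article, that student sleep shifts in that period, for example around holidays or examinations. If it does, the time-by-group term can pick up the calendar as well as the programme.

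The limitations in section 3 cover sample size, contamination and device availability, but neither of these points.

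**Working it through.** **Order of events.** Set side by side, sections 2.7 and 2.3.5 give: consent, random assignment, preference split of the intervention arm only, baseline, sessions, post assessment, with unblinded participants. The moment of disclosure is not stated. A preference split confined to the intervention arm and placed before baseline makes earlier disclosure the natural reading, and no sentence rules it out.

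**Effect of an arm-dependent baseline.** Suppose knowledge of the arm shifts one arm's baseline mean by b0 and the shift does not persist to the post measure.
- Group-by-time contrast: the bias is −b0, one for one.
- Model with baseline as covariate: the bias is −β·b0, where β is the slope of post on baseline. It is smaller but not zero.

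**Device arithmetic.** Inputs: 60 students (abstract), 2 measurements each (2.5.1), one week per measurement, 10 devices (2.7).
- Student-weeks of wear: 60 × 2 = 120.
- Calendar weeks of measuring: 120 / 10 = 12, that is 6 per wave, or 3 per arm per wave.
- Stated duration: 16 weeks. This is reached as 12 + 4 session weeks, or as 12 + 2 session weeks + 2 recruitment weeks. The figure is feasible, but the text does not give its split, so it is neither confirmed nor refuted.

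**Gap between arms within a wave.** One subgroup of 10 (2.4) takes all ten devices, leaving none for controls that week.

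| Schedule within a wave | Intervention weeks | Control weeks | Gap in mean week |
|---|---|---|---|
| Arms in blocks | 1, 2, 3 | 4, 5, 6 | 5 − 2 = 3 |
| Groups of 10 alternate | 1, 3, 5 | 2, 4, 6 | 4 − 3 = 1 |
| 5 + 5 mixed each week | 1 to 6 | 1 to 6 | 0 |

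**When the gap becomes bias.** The contrast is (post − pre) in one arm minus (post − pre) in the other.
- A calendar difference of the same size at both waves cancels.
- An event of 0.3 SD (assumed) that hits 1, 2 or 3 of one arm's three post weeks, and nothing else, gives a bias of 0.3 × k/3 = 0.10, 0.20 or 0.30 SD.
- A drift of 0.05 SD per week (assumed) gives 0, 0.05 or 0.15 SD if the arms' pre-post intervals differ by 0, 1 or 3 weeks.

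**Effect on the test.** With 30 per arm, two-sided 5% (sidedness assumed) and a bias of s SD of the change score, the t statistic has 58 degrees of freedom and noncentrality s / √(2/30).

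| s | Noncentrality | Chance of rejecting a true null |
|---|---|---|
| 0.1 | 0.387 | 6.7% |
| 0.2 | 0.775 | 11.9% |
| 0.3 | 1.162 | 20.8% |

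If the bias is expressed in SD of the outcome itself, the change score has SD √(2(1 − r)), where r is the pre-post correlation. At r = 0.5 this equals 1 and the table is unchanged. At r = 0.7 the rates are 7.8%, 16.6% and 31.4%. A bias in the other direction would hide a benefit instead.

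**The case against.** The best defence is that the week plan is in Figure 2, which is not available here. Groups in the staggering sentence could mean the arms or the intervention subgroups, and a figure that mixes arms within weeks would remove the calendar problem. This stands. A reader might infer that arm and calendar time are confounded as a matter of fact and that no analysis could separate them. The text does not support that: full aliasing requires a particular schedule, alternating groups would leave a gap of only one week, and level differences common to both waves cancel.

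Second, disclosure before baseline is inferred. Session preferences could have been collected from everyone at consent, and section 2.3.4 keeps the sequence hidden from the other researchers. This also stands as a caution. A reader should not take it as stated that students know their arm at baseline. But hiding the sequence from researchers is not a promise to withhold the arm from students, and the order in section 2.7 points the other way.

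Third, the size of any calendar shift has no anchor in the article. This is correct, and the rates above are illustrations only. The device shortage also constrains the wrist monitor, not the PSQI, so the calendar argument reaches the PSQI only if the questionnaire is given with the device week. The baseline-order argument applies to both outcomes, and most strongly to the PSQI.

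Pilot status does not dispose of the point, since section 4 aims to show a positive effect and section 3 would use the data to seek funding for a larger study.

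**Conclusion.** The point holds in two parts of unequal certainty.

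The firmer part is the order. Baseline follows allocation in an unblinded trial, with no safeguard stated. This rests on the text of sections 2.7 and 2.3.5 and does not depend on Figure 2.

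The calendar part is conditional. It holds if groups of 10 are measured whole, which is the natural reading of the text, and if events differ between waves or pre-post intervals differ by arm. Under those conditions the illustrative false-positive rate is about 7% to 21% for biases of 0.1 to 0.3 SD of the change score. Both the biases and the calendar effects behind them are assumed.

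Device scarcity does not force either problem, because a mixed schedule uses the same 12 measuring weeks. The change should be made, and confidence in the point is medium.

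**What to change.** 1. Collect session preferences from every student at consent.
2. Run the devices in six batches of 10 students. Complete each student's baseline PSQI and device week before the arm is assigned or disclosed.
3. Have the independent researcher then randomise 5:5 within the batch, using blocks matched to batches.
4. Measure both arms of a batch in the same post week, with the same pre-post interval, and tie the control PSQI to that week. Section 2.5.1 times the second PSQI immediately after the intervention, which is undefined for controls.
5. Include batch in the analysis.
6. State the week plan in the text as well as in Figure 2.

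**Feasibility.** If batch b has baseline in week b and its post measurement in week b + 6, the six batches use weeks 1 to 6 and 7 to 12. Each week uses ten devices, and every student has a six-week interval. That leaves 16 − 12 = 4 weeks of slack.

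**Cost.** No extra device or measuring week is needed, but this is more than a change of wording. Each batch yields five intervention students, so two batches must be pooled to form a session group of 10. The first batch of each pair then waits about a week longer between baseline and sessions. With equal pre-post intervals, the second batch is measured about a week later after its sessions. Allocation is also released in batches rather than all at once.

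One inconsistency must be settled first. Section 2.4 describes two subgroups of 10, which makes 20, while the abstract gives an intervention group of 30. The passages must be reconciled before any week plan can be fixed.
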